## **S1 Appendix. Study Protocol for Ethics Application**

### **EFFECT OF UPPER LIMB ISOMETRIC TRAINING ON HAMSTRING STRENGTH IN EARLY POSTOPERATIVE ANTERIOR CRUCIATE LIGAMENT RECONSTRUCTION PATIENTS: A RANDOMISED CONTROLLED TRIAL**

#### **Abstract**

This study aims to investigate the effects of upper limb isometric training (ULIT) combined with standard care of an anterior cruciate ligament reconstruction (ACLR) rehabilitation program on hamstring strength and physical function in the early-phase postoperative period. Early recovery of hamstring strength is critical for knee stability and functional rehabilitation post-ACL surgery. Hamstring strength deficits are prolonged issues in rehabilitation, with significant hamstring strength deficiencies in an early postoperative ACLR, especially using hamstring autograft, leading to functional limitations and an increased risk of secondary injuries. High knee muscle strength imbalances can hinder strength return in later stages. However, swelling, donor site pain, joint stiffness, and graft protection often neglect the direct activation of the hamstring in the early period. Also, clinical practice guidelines and consensus on early rehabilitation strategies are conflicting. While lower limb strengthening exercises are the mainstay of rehabilitation, this study explores the potential benefits of ULIT in promoting hamstring activation through the inter-limb posterior myofascial kinetic chain. This study hypothesise that participants receiving ULIT in addition to standard care will demonstrate better hamstring strength at 12 weeks post-operatively compared to those receiving standard care rehabilitation alone. A total of 32 patients who underwent ACLR with hamstring tendon autografts will be randomly assigned to either the ULIT group or a control group. The ULIT group performed upper limb isometric exercises in addition to standard postoperative rehabilitation, while the control group followed the standard rehabilitation protocol alone. We will measure hamstring and quadriceps strength using hand-held dynamometry at baseline (preoperative), 4, 8, and 12 weeks postoperatively. The primary outcome is the change in hamstring strength in the operated limb, while secondary outcomes included hamstring flexibility and patient-reported outcomes on symptoms, physical function and adherence. Statistical analysis will be conducted to compare the strength recovery between the two groups. It is believed that the results of this study will enhance knowledge about the global functional muscle concept, offer effective, safe, inexpensive, and feasible interventions, and promote further research on the interlimb connection of muscle activation and flexibility in heterologous muscle groups after ACLR.

**Keywords:** isometric training, hamstring, anterior cruciate ligament, rehabilitation.

## Background and Literature Review

Anterior Cruciate Ligament (ACL) injuries are common in sports, with a prevalence of 68.6 per 100,000 individuals per year (Matar et al., 2021). ACL reconstruction (ACLR) is indicated for those who are physically active and experience prolonged knee instability (Hiemstra et al., 2000). Over 100,000 ACLRs were performed worldwide, with an annual increase of at least 2% in the past decade (Zbrojkiewicz et al., 2018). The ACLR significantly impacts physical function and keeps the patients out of sports for at least six months (Kuenze et al., 2023). The prevalence of knee weakness, tightness, and physical function limitation in post-ACLR patients have been associated with demographic factors, duration from injury to surgery, concomitant bone and chondral lesion, type of graft and surgical technique, and timing and structure of rehabilitation program (Fairus et al., 2022; Herbawi et al., 2022; Roula et al., 2023). The ACLR may result in chronic neuromuscular inhibition and persistent hamstring strength deficits, especially when using an ipsilateral hamstring autograft (San Jose et al., 2023). Around 50% hamstring strength deficit was observed in patients with hamstring tendon graft at 4 weeks, and only 46% achieved a knee flexor limb symmetry index (LSI) >90% at 6 months, compared to 67% with patellar tendon graft (Forelli et al., 2023; Zumstein et al., 2022). Knee flexor weakness deficits can be significant during the return to sport (RTS) phase at 6 months and even over a year following the ACLR (Lee & Lee, 2020). Chronic hamstring strength deficiencies following ACLR increase the risk of ACL re-injury, changes in running mechanics, negative self-reported outcomes, and a higher likelihood of post-traumatic osteoarthritis (Herbawi et al., 2022; Högberg et al., 2024; San Jose et al., 2023). Despite a significant increase in ACLR, no recent studies have reported whether the prevalence of ACLR cases among the Malaysian population aligns with those reported in current literature worldwide.

Restoring knee flexor muscle function is crucial for ACL rehabilitation, as the hamstring muscles contribute to knee joint stability by preventing excessive ACL shear stresses (Ko et al., 2012; San Jose et al., 2023). Anatomically, the medial hamstrings reduce medial condyle liftoff and dynamic knee valgus, known risk factors for ACL injuries. Knee flexor weakness increases the chance of ACL re-injury (Rob et al., 2018). Impaired knee flexor function following ACLR using a hamstring graft is often caused by complications related to the donor site (San Jose et al., 2023). A severe grade 4 injury of the harvested semitendinosus tendon can lead to decreased hamstring muscle activation during eccentric contraction (Forelli et al., 2023; Kositsky et al., 2022). Regeneration of the tendon may take around 18 months in 10-50% of patients (Lee & Lee, 2020). If these deficiencies are not counterbalanced early by hamstring hypertrophy and activation, they can result in a chronic deficiency in knee flexion strength (Fukunaga et al., 2019). Additionally, the absence of compensatory hypertrophy in the medial hamstring muscles can result in deficiencies in the overall volume of the hamstring muscles, impacting knee control and worsening the imbalance in muscular strength around the knee (Labanca et al., 2022).

Early-phase rehabilitation from the first week up to 3 months (see Figure 1a), postoperative aims to alleviate pain, reduce swelling, restore knee joint range of motion and optimize muscle strength, regain daily activities like walking without crutches, and minimize

muscle atrophy (Roula et al., 2023). There is typically a 50% decrease in knee flexor isometric strength after 4 weeks (Harput et al., 2015). This decrease in strength often aligns with the transition from the early to mid-rehabilitation phase. At three months post ACLR, recovery in quadriceps strength was 82% and recovery in hamstring strength was 76% following a structured neuromuscular rehabilitation (Harput et al., 2015; McPherson et al., 2023). A high prevalence of knee muscle strength imbalances would impede the return of strength throughout the latter stages of rehabilitation (Ohji et al., 2022). However, direct activation and stretching of the hamstring in the early period, especially the first 12 weeks after ACLR rehabilitation, is often neglected and challenging because of swelling, donor site pain, joint stiffness and the necessity to protect the graft from excessive tensile force and joint loading (Cristiani et al., 2021). In post-operative ACLR, a neurological response known as Arthrogenic Muscular Inhibition (AMI) disrupts sensory information transmission, leading to dysfunction in the somatosensory and motor cortex (Pietrosimone et al., 2022). This inhibits quadriceps and hamstring activation due to a cortical reflex (Pinto et al., 2017; Sonnery-Cottet et al., 2022). Instead, there are limited clinical practice guidelines (CPG) and consensus on hamstring strength and flexibility rehabilitation strategy in the early stage following ACLR (see Figure 1a), with most of the studies in ACL prevention and rehabilitation focusing on gaining quadriceps strength and achieving full knee extension, which overshadows the need for strengthening and flexibility of hamstring (Roula et al., 2023; Svantesson et al., 2020). Despite that, restoring optimal hamstring strength is an important facet of functional recovery following ACLR, providing dynamic joint stabilization and preventing excessive ACL shear forces during forceful dynamic movement (San Jose et al., 2023). Thus, it is necessary to achieve optimal hamstring strength during the initial stage of the ACLR rehabilitation programme before progressing to the next phase.

The myofascial kinetic chain is a crucial part of functional anatomy, consisting of interconnected muscles and connective tissues (Myers, 2014; Stecco et al., 2023). The ULIT like shoulder abduction, external rotation, or scapular retraction can work out muscles in the posterior myofascial kinetic chain (PMKC), including the hamstrings (Deng et al., 2022; Nuhmani & Zouhal, 2022). This approach enhances neuromuscular coordination and movement efficiency, integrating hamstring muscles into functional activities and dynamic motions. The ULIT indirectly loads the hamstring muscles through their connections along the kinetic chain, enhancing muscle activation, joint stability, and movement efficiency, rendering isometric training a potentially efficacious rehabilitation intervention.

To maximize the strength benefits of inter-limb cross effect, it is recommended to train with a resistance level of at least 50% of one's maximum voluntary strength, as this intensity has been proven to yield significant strength gains (Smyth et al., 2023). The ULIT has the potential to serve as a warm-up before engaging in physical activities, as it stimulates interlimb muscle activation and enhances the body's preparedness for dynamic physical and sports activities (see Figure 3). Therefore, isometric contraction of the upper limb could be advantageous in injury prevention and early rehabilitation stages.

Muscle synergies play a pivotal role in optimizing hamstring strength and function in ACL reconstruction patients (Saki et al., 2023; Zumstein et al., 2022). The PMKC framework emphasizes the significance of these synergies in improving neuromuscular coordination and movement efficiency. Isometric exercises that target the musculature of the upper limb can enhance hamstring strength and functional results by improving knee muscle coordination and

[figure not shown]

**Figure 1b:** ACLR Clinical Practice Guideline (Aspetar, 2023).

[figure not shown]

**Figure 3:** Proposed Mechanism and Exercises of ULIT.

## **Problem Statement**

Considerable hamstring strength deficits following ACLR impact patients' physical function and increase re-injury risk. The high prevalence of hamstring strength imbalances in early-phase ACLR rehabilitation, particularly with hamstring autografts, hinders recovery. Early postoperative ACLR challenges, such as swelling, donor site pain, and joint stiffness, complicate direct hamstring activation, eccentric loading, and stretching. This study aims to investigate the effect of specific upper limb isometric training (ULIT) combined with standard care rehabilitation on hamstring strength and physical function in early-phase postoperative ACLR patients, potentially offering a novel and effective approach to ACLR rehabilitation.

## **Research Significant and Benefits**

Applying exercise to the unaffected limb can offer an alternative, feasible and novel approach for acute stage and early rehabilitation of ACLR. Initiating indirect training in the non-injured limb allows muscle activation without causing unnecessary pain and complications to the injured part. This approach may accelerate return to achieve optimal strength and physical function enhancement among post-operative ACLR patients.

## **Research Question**

Does the combination of upper limb isometric training (ULIT) and a standard care rehabilitation protocol enhance hamstring strength among patients in the early postoperative phase of ACLR?

## **Research Objective**

The main objective of this study is to investigate the effects of upper limb isometric training (ULIT) combined with standard care rehabilitation versus standard care rehabilitation alone on hamstring strength and physical function in early phase postoperative ACLR patients.

The secondary objectives are:

- 1) to assess the efficacy of ULIT compared to standard care in improving physical function three months after surgery.
- 2) to explore ULIT's effectiveness in enhancing hamstring flexibility at three months following ACLR
- 3) to assess patient adherence to ULIT.

## **Specific Objectives**

1. To investigate the difference in hamstring strength between the ULIT and the standard care group compared to the standard care alone group at 4, 8, and 12 weeks post-ACLR.
2. To measure the changes in physical function based on the IKDC score in the ULIT group compared to the standard care group at preoperative and 12 weeks post-ACLR.
3. To evaluate the effect of ULIT on hamstring flexibility, measured by the active knee extension test (AKET) test, compared to standard care alone at preoperative and 12 weeks post-ACLR.
4. To analyse the relationship between patient adherence to ULIT and improvements in hamstring strength and physical function over the 12-week rehabilitation period.

## **Research Hypothesis**

We hypothesise that participants receiving the ULIT plus standard care will have better hamstring strength at 12 weeks post-operatively compared to participants receiving a standard care rehabilitation program alone.

### *Null Hypothesis*

There is no significant difference between the combination of ULIT and standard care rehabilitation compared to the standard care rehabilitation alone on hamstring strength in early phase ACLR.

### *Alternative hypothesis*

The combination of ULIT and standard care rehabilitation significantly improves hamstring strength compared to standard care rehabilitation alone in early phase ACLR

## **Methods**

The methods are reported following CONSORT guidelines for non-pharmacological treatment studies and the Template for Intervention Description and Replication (TIDieR) reporting of interventions.

## **Study Design**

This is a longitudinal, parallel-group, concealed allocation, randomised (1:1) controlled, single-blinded (assessor) study conducted at a tertiary hospital. If participants satisfy the eligibility criteria, provide informed consent, and have completed baseline measurement testing, they will be randomly assigned to the study. Participants will be informed that they will be randomly

assigned to one of two study groups: 1) the intervention group (ULIT plus standard care ACLR rehabilitation protocol) or 2) the control group (standard care rehabilitation protocol).

### **Study setting**

The trial will be carried out at the Orthopaedic Clinic and Physiotherapy Unit of Hospital Canselor Tuanku Muhriz (HCTM). The majority of recruited participants will be located in the Klang Valley, where they will receive surgical care from the same team. The main distinction among them will be the source of funding and reimbursement for their surgeries. The project will seek ethics approval from the Institutional Review Board (IRB) at the Research Ethics Committee UKM (RECUKM). The trial will be done in compliance with the Declaration of Helsinki (2000) and will be registered with the Australian and New Zealand clinical trials registry (<http://www.anctzctr.org.au>).

### **Eligibility**

Potential participants who meet the criteria for the study will receive an invitation to participate no later than two weeks prior to their ACLR surgery. The potential participants will be identified based on the elective operation list of the Orthopaedic Clinic of HCTM. The patients who meet the specified criteria will be provided with both oral and written information regarding the trial's conditions and will be required to sign a standardised consent form. The principal investigator will verbally present information about the trial to eligible participants. The inclusion criteria will be verified based on the patient's written medical records physical examination by the surgeon and through direct communication with the patient. Patients who choose not to participate in the trial will still receive standard care rehabilitation.

### **Inclusion/Exclusion Criteria**

The inclusion criteria are as follows: individuals who plan for ACLR using a ipsilateral hamstring tendon autograft, with or without a meniscal injury, capable of understanding English and giving informed consent, and are aged between 18 to 45 years. The following factors are considered as exclusions: Individuals with a revision ACL surgery, a multi-ligament injury (such as instability in the collateral, posterolateral, medial, or posterior cruciate ligaments), the use of allografts, an upper limb and contralateral lower limb injury after ACL surgery.

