## **Randomisation and Allocation**

Following the baseline assessments, individuals will be assigned either to the intervention group or the control group by a simple random sampling. The randomisation process will be performed using a computer-generated sequence numbering scheme ranging from one (1) to thirty-two (32), with an equal allocation ratio of 1:1. The concealment is achieved using a set of sealed and numbered envelopes. Allocation takes place following baseline testing (T1), when a staff of the Orthopaedic Department, who is not participating in the study, opens the next study envelope. Subsequently, they notify the group assignment to the attending physiotherapist. The envelopes will be securely stored and sealed in a cabinet to ensure security and prevent any unauthorised access. Measures will be implemented to restrict the number of authorised individuals who have access or authority to open the research envelopes, to prevent any potential bias in the allocation process. The statistical analysis will specifically focus on allocation codes, ensuring that the data analyzers remain unaware of the study group allocation (see Figure 9).

[figure not shown]

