### **Data Collection**

The study will collect demographic data, as well as pre-, intra-, and postoperative data (see Table 3). Data will be gathered from the participants and their medical records for all the data collection forms (see Appendix A, C, and D). Baseline evaluations will be conducted throughout the pre-operative period, within a range of 14 days, to reduce any bias when selecting participants. The subsequent assessment in the 4th week ( $\pm 14$  days), 8 weeks ( $\pm 14$  days), and three months ( $\pm 14$  days) are scheduled at the Orthopaedic Clinic (van Melick et al., 2021). The blinded assessors will give all tests and questionnaires in person, ensuring participant consistency. These assessments will take place at four weeks, eight weeks and three months after the surgery. Phone consultations will be used for post-hospital discharge follow-up. Participants who cannot be reached by phone for a continuous period of 14 days starting from the assessment due date will be classified as lost to follow-up for outcome measurement.

intra-reliability had a value of 0.9269 [95% C.I.: 0.8909–0.9533] (Grgic et al., 2020; Karagiannopoulos et al., 2022; Romero-Franco et al., 2019).

The participants are directed to generate deliberate isometric contractions of their quadriceps or hamstring muscles, by pushing against the resistance provided by the dynamometer's arm with a perceived maximal effort of 100% (Grgic et al., 2020). During the formal testing, the participants conducted three maximum voluntary isometric contractions (MVIC) of knee extension lasting five seconds each for the quadriceps (Padulo et al., 2020). Similarly, This is followed by knee flexion testing for the hamstrings. A minute rest time will be given between the quadriceps and hamstring testing (Mellemkjær et al., 2024).

The assessor will consistently give instruction and verbal encouragement (see Appendix I). The participants are instructed to exert maximum force by either pushing with their quadriceps or pulling with their hamstrings against the dynamometer. The average and best scores of the peak forces will be recorded (Grgic et al., 2020).

The average scores of quadriceps and hamstring muscular strength during rehabilitation are quantified using the Quadriceps Index (QI) and Hamstring Index (HI), which are calculated using the formula:  $(\text{MVIC peak force of the affected limb} / \text{MVIC peak force of the unaffected limb}) \times 100$  (van Melick et al., 2021).

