## Sample Size

Sample size calculations are performed using SPSS version 29 for the primary outcome: differences between two means of Hamstring MVIC peak force symmetry index (see Figure 11). With the population standard deviation for the main outcome measure amount of 0.71 as in the Harput et al. study, type I error of 0.05, type II error of 0.2, 80% power, the minimum sample size required is 14 patients per group (28 in total). Expecting an attrition rate of 10%, 16 participants are considered for each study group.

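### The limb-injury exclusion is tied to injuries after surgery, so it does not screen out a previously injured opposite leg, which is the denominator of the Hamstring and Quadriceps Index

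*Protocol*

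**What the plan says.** **Who is excluded.** Under Inclusion/Exclusion Criteria the protocol admits "individuals who plan for ACLR using a ipsilateral hamstring tendon autograft, with or without a meniscal injury", subject to language, consent and age. It excludes "Individuals with a revision ACL surgery, a multi-ligament injury", allograft use, and "an upper limb and contralateral lower limb injury after ACL surgery". Nothing else there concerns the opposite leg or the arms.

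**When eligibility is settled.** Under Eligibility, candidates "will receive an invitation to participate no later than two weeks prior to their ACLR surgery". Under Randomisation and Allocation, the envelope is opened once baseline testing is complete, and the Abstract and Data Collection place that testing before the operation.

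**Where the opposite leg enters the data.** Data Collection defines both indices as the affected limb's peak force divided by that of the limb labelled unaffected, times 100. Sample Size describes the outcome used for sizing as "differences between two means of Hamstring MVIC peak force symmetry index". The Abstract words the primary outcome as the operated leg's strength change, and Statistical Analysis as the week 4 to week 12 change in isometric hamstring force; neither has a contralateral denominator. Statistical Analysis then adds a within-group repeated-measures analysis of the two indices, and a repeated-measures analysis of rehabilitation and time for all measured variables.

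**The concern.** An exclusion criterion has to be decidable when eligibility is decided. For the operation under study, an injury after surgery has not yet happened at screening or at allocation, so this criterion excludes nobody at entry. A patient whose other knee was reconstructed earlier, or whose other hamstring was injured earlier, is eligible on the text. Revision surgery ordinarily means a repeat operation on the same knee, and the multi-ligament criterion does not name the opposite leg.

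The index formula assumes what the criteria do not secure: that the reference leg is sound. If it is weak, the ratio rises and an unrecovered operated leg looks more symmetrical than it is. The Background itself says knee flexor weakness can still be significant more than a year after reconstruction, so an earlier operation on the other side could plausibly leave a weak denominator. With 14 to 16 patients per arm, a few such patients can move an arm mean.

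On one reading, the time limit also covers the upper limb part, so an existing upper limb injury would not bar entry to a trial whose intervention is three upper limb exercises.

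**Working it through.** **Step 1: does any criterion close the gap?** There are three ways to read the phrase.

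- The time limit qualifies both parts. Neither a previous contralateral leg injury nor an existing upper limb injury is then excluded.
- The time limit qualifies only the leg part. Upper limb injury is then excluded at any time, but the contralateral gap remains.
- The surgery meant is any earlier ACL operation. Contralateral injuries unrelated to such an operation are still admitted.

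The contralateral gap survives all three readings; the upper limb gap appears only under some.

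**Step 2: inputs.** The table reprinted under Sample Size (Figure 11) gives mean hamstring torque in Nm/kg:

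- week 4: involved 1.0, uninvolved 1.86;
- week 12: involved 1.55, uninvolved 2.05.

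The documents give no contralateral deficit *d*. I assume a range of 10% to 24%. The upper end borrows the three-month shortfall implied by the Background ("recovery in hamstring strength was 76% following a structured neuromuscular rehabilitation"). That figure belongs to a recently operated leg, so it is an illustration and not an estimate.

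**Step 3: reproduce the protocol's figure.** HI at week 12 = 1.55 / 2.05 = 75.6%, in line with the quoted 76%. HI at week 4 = 1.0 / 1.86 = 53.8%. The gain is 21.8 points. These are ratios of means, used only to set the scale.

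**Step 4: weaken the reference leg.** With true torques I (involved) and U (uninvolved), observed HI = 100 × I / [U × (1 − d)], and the error is observed HI minus true HI.

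| | d = 10% | d = 24% |
|---|---|---|
| Week 12 HI | 1.55 / (2.05 × 0.90) = 84.0% | 1.55 / (2.05 × 0.76) = 99.5% |
| Error at week 12 | 8.4 points | 23.9 points |
| Week 4 HI | 1.0 / (1.86 × 0.90) = 59.7% | 1.0 / (1.86 × 0.76) = 70.7% |
| Error at week 4 | 6.0 points | 17.0 points |
| Error in week 4 to 12 change | 8.4 − 6.0 = 2.4 points | 23.9 − 17.0 = 6.9 points |

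A stable deficit raises both time points, so much of it cancels in the change.

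**Step 5: effect on an arm mean of 14 (one such patient).**

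- Week 12 level: 8.4 / 14 = 0.6 to 23.9 / 14 = 1.7 points.
- Week 4 to 12 change: 2.4 / 14 = 0.2 to 6.9 / 14 = 0.5 points. Against the 21.8-point gain, the upper end is 0.5 / 21.8, about 2%.

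Two such patients in the same arm double these figures.

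**Step 6: direction.** Allocation is random, so such patients are equally likely in either arm and the expected error in the between-group difference is zero. What remains is extra variance and chance imbalance.

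**The case against.** The strongest reply is that the primary outcome does not use the opposite leg. The Abstract and Statistical Analysis both word it as strength or force of the operated limb, and the indices appear there as a further analysis. The table behind the sample size reports torques, with no standard deviation for an index. This stands, with one reservation: Sample Size explicitly calls the symmetry index the primary outcome, and the protocol does not reconcile the two. A reader might infer that the gap invalidates the primary endpoint; the documents do not support that.

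Second, a reader might set the 12-week shifts of 1.7 points (one patient) and 3.4 points (two patients) against the 21.8-point gain and call them about 8% and 16% of it. That divides an error in a level by a change. On the same inputs, the error in the change is 0.5 points on the arm mean for one patient. The larger figures apply only to a 12-week comparison of HI levels. That comparison is not irrelevant, since the Research Hypothesis speaks of strength at 12 weeks, but it is a different quantity.

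Third, the documents give no frequency for previous contralateral injury and no deficit for it. Nor do they say that such a deficit never fades; the Background says only that weakness can be significant at those times. All of this stands, and it is why the sizes are conditional.

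Fourth, the upper limb part depends on how an ambiguous phrase is read. Requiring both injuries together because they are joined by the word and would be an uncharitable reading of a list of exclusions. A reader might also infer that such a patient could not do the exercises safely; the documents say nothing on that.

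None of this restores a criterion that can work at screening.

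**Conclusion.** The point holds as a fault in a stated rule. The criterion describes an event that lies after the moment at which it must be applied, and no other criterion makes the reference leg of the indices a sound one. The authors may have intended to exclude previous injury, but the wording does not do so.

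The consequence is modest. It falls on the Hamstring and Quadriceps Index, and on the primary outcome only if that is the symmetry index. It adds noise and possible chance imbalance in a small trial; it does not bias the comparison systematically. The sizes in the working rest on an assumed 10% to 24% contralateral deficit that is stable over weeks 4 to 12, on ratios of the cited cohort's means, and on at least one such patient enrolling. The text permits such a patient; it does not show that any will enrol. The change is worth making because it is cheap and protects a measured outcome, not because the trial fails without it.

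**What to change.** Reword the criterion so that it applies at screening and separates the two limbs: exclude a previous or current significant injury or surgery of the contralateral lower limb, **or** a current upper limb injury. Name previous contralateral ACL reconstruction and hamstring injury explicitly as examples, so that the revision-surgery criterion is not relied on to cover them. Verify it with the checks already listed under Eligibility: the medical record, the surgeon's examination and direct contact with the patient.

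Remove the reference to injuries after surgery from the exclusion list. Record such injuries as post-randomisation events and keep those patients in the intention-to-treat analysis that the protocol already promises under Intervention Fidelity, Blinding and Statistical Analysis.

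The cost is one sentence in the eligibility section and a few patients who become ineligible. Recruitment from a list of three to four cases a month would slow slightly.
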